### Plans to give access to the full protocol, participant-level data, and statistical code {31c}

Statistical codes are available upon request.

### Oversight and monitoring

#### Composition of the coordinating center and trial steering committee {5d}

The Ethics Committee of Guilin People’s Hospital will supervise all the study stages. They will oversee the conduct of the trial at any unexpected time and will issue recommendations for early termination, modifications, or continuation of the trial, if necessary.

#### Composition of the data monitoring committee, its role, and reporting structure {21a}

This single-center study did not require a data monitoring committee.

#### Adverse event reporting and harms {22}

Any adverse events and other unexpected accidents during the study period will be recorded and reported to the Ethics Committee of Guilin People’s Hospital for decision-making.

#### Frequency and plans for auditing trial conduct {23}

The Ethics Committee will be responsible for monitoring the trial. Audits on accuracy may be carried out at any time and at least twice.

#### Plans for communicating important protocol amendments to relevant parties (e.g., trial participants, ethical committees) {25}

Protocol amendments will be approved by the Trial Steering Committee, and the ChiCTR.org.cn listing will be updated periodically for enrollment or major protocol changes.

#### Dissemination plans {31a}

The final study results will be published in international peer-reviewed journals focusing on the investigatory field in question.

## Discussion

The plasma membrane of sperm contains rich polyunsaturated fatty acids (PUFAs), which are extremely vulnerable to attack by ROS and eventually lead to lipid peroxidation and the formation of MDA. The level of seminal plasma MDA can reflect the production of oxygen free radicals in seminal plasma and the degree of causing lipid peroxidation, while TAC reflects the reduction potential in seminal plasma. Seminal plasma MDA and TAC are important indicators for the diagnosis and treatment of male infertility, have a clear correlation with the sperm quality of male infertility, and affect sperm quality under the regulation of antioxidant treatment [27–29]. Many uncontrolled oxidative stress factors, such as inflammatory reactions, bacteria, or viruses, may have an impact on male testes or reproduction [27, 30, 31], and thus, there seems to be a wide demand for antioxidant supplements in male reproduction. However, reducing stress may also be related to excessive supplement of antioxidants, and may aggravate ROS production, thus affecting sperm quality [32]. This requires us to examine the necessity of antioxidant supplementation.

Some animal experiments have shown that ALA supplementation can alleviate ROS, reduce testicular tissue damage, and improve testicular spermatogenesis and steroidogenesis disorders [33–36]. A small number of clinical studies have also found that ALA supplementation can improve the quality of semen parameters in male infertility [37, 38], and there are also fewer studies on the application of ALA in varicocele-related male infertility [23, 24]. Previous studies have mostly focused on surgical treatment of varicocele-related male infertility or postoperative supplementation with antioxidants, while this clinical trial intends to study both surgical and non-surgical treatment of varicocele-related male infertility patients and compare the effects of two antioxidants (ALA vs. vitamin E) on semen parameters, seminal plasma MDA and TAC before and after treatment, so as to reveal whether antioxidant use is necessary for varicocele-related male infertility, how potent should be used, non-surgical application, or postoperative application. Since our study involved surgical and non-surgical treatment options, some non-surgical patients are likely to choose further treatment options (varicocelectomy) after finishing the trial, which is also what we may recommend and according to the patient’s wishes. We may continue to follow up these patients who underwent surgery after antioxidant treatment.

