**Methods:**

In this randomized controlled clinical trial, we will randomize 80 patients with varicocele-related male infertility from Guilin People’s Hospital. The non-surgical observation group (*n* = 20) will receive ALA, the non-surgical control group (*n* = 20) will receive vitamin E, the surgical observation group (*n* = 20) will receive ALA after the operation, and the surgical control group (*n* = 20) will receive vitamin E after the operation. The course of treatment will be 3 months. The results will compare the changes in semen parameters, sex hormones, testicular volume, sperm DNA fragment index (DFI), seminal plasma malondialdehyde (MDA), and total antioxidant capacity (TAC) between the groups at baseline and after 3 months of antioxidant supplementation.

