**Discussion:**

Whether it is necessary to use antioxidants in varicocele-related male infertility, how potent antioxidants should be used, postoperative application or non-surgical independent application still needs to be explored. This study attempts to compare the effects of two antioxidants (ALA and vitamin E) on sperm quality in patients with varicocele-related male infertility (surgical or non-surgical) and attempted to answer the above questions.

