### Objectives {7}

The general objective is to determine the efficacy and significance of ALA in varicocele-related male infertility through a randomized controlled clinical trial.

The specific objective is to determine the effect of different intensities of antioxidant conservative and surgical treatment of varicocele on sperm quality of varicocele-related male infertility patients by comparing surgical and non-surgical supplementation of ALA or vitamin E.

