#### Intervention description {11a}

In the four groups, the non-surgical observation group will take a lipoic acid capsule 0.6 g, once a day; the non-surgical control group will take a vitamin E soft capsule 100 mg, twice a day; the surgical observation group will take a lipoic acid capsule 0.6 g, once a day; the surgical control group will take an oral vitamin E soft capsule 100 mg, twice a day. The course of treatment will be 3 months.

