## Statistical methods

### Statistical methods for primary and secondary outcomes {20a}

Data analysis will be performed using IBM SPSS Statistics for Windows, version 24 (IBM Corp., Armonk, NY, USA). Compliance of variables with normal distribution will be analyzed by the Shapiro-Wilk test and homogeneity of variance by Levene’s test. Continuous variables will be expressed as mean with standard deviation (mean ± SD) or median (25 to 75%). Categorical variables will be expressed as numbers with percentages. Continuous data that are normally distributed and homogeneous in variance will be analyzed with one-way analysis of variance, and if the result is statistically significant, multiple comparisons will be performed with Bonferroni correction. Continuous data that do not obey normal distribution or have unequal variance will be analyzed with the Kruskal-Wallis test, if the result is statistically significant, then the Wilcoxon signed-rank test, with a Holm-Bonferroni method correction for multiple comparisons. Within groups before and after the intervention will be analyzed by paired-samples *t*-test for normally distributed variables and Wilcoxon signed-rank test for non-normally distributed variables. Categorical data will be analyzed using Pearson’s chi-square test or Fisher’s exact test. The level of significance will be set to *p* < 0.05.

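### The trial cannot show whether antioxidants are necessary, because all four arms receive one; on potency it can only rank two fixed regimens

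*Protocol article*

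**What the plan says.** The main Discussion states what the comparison of ALA and vitamin E, surgical and non-surgical, is for: "so as to reveal whether antioxidant use is necessary for varicocele-related male infertility, how potent should be used". The Discussion paragraph of the Abstract opens with the same questions, "Whether it is necessary to use antioxidants in varicocele-related male infertility, how potent antioxidants should be used", and says, less firmly, that the study "attempted to answer the above questions".

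The arms are fixed in Intervention description {11a} and in the Methods paragraph of the Abstract. Without surgery, "the non-surgical observation group will take a lipoic acid capsule 0.6 g, once a day" and "the non-surgical control group will take a vitamin E soft capsule 100 mg, twice a day". The two surgical arms take the same two regimens after the operation; for example, "the surgical control group (*n* = 20) will receive vitamin E after the operation". The section on the choice of comparators {6b} itself describes vitamin E as an antioxidant.

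Statistical methods {20a} plans a four-group comparison with pairwise follow-up. It adds tests inside each arm: "Within groups before and after the intervention will be analyzed by paired-samples" t-test, or by the Wilcoxon signed-rank test where the data are not normal.

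The specific objective in Objectives {7} is narrower. It is "to determine the effect of different intensities of antioxidant conservative and surgical treatment of varicocele on sperm quality", pursued by comparing ALA or vitamin E with and without surgery. It does not mention necessity.

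**The concern.** Whether antioxidants are needed is a question about antioxidant versus no antioxidant. Answering it takes men who receive none, with surgery or without. The design has none, so the contrast named in the Discussion is not among those the trial can estimate, whatever its size or analysis.

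The only planned analyses that seem to speak to an absolute effect are the before-after tests. A significant rise in an arm could be taken as evidence that the antioxidant works and is needed, although surgery, time or regression to the mean could produce it. This matters because the question is open in the protocol's own account. Background and rationale {6a} cites a meta-analysis in favour of adjuvant medical therapy after varicocelectomy. It also cites newer evidence of no benefit, in operated or non-operated men, when oxidative stress was not screened for beforehand.

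**Working it through.** **1. Which contrasts the four arms give**

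| | ALA 0.6 g once daily | Vitamin E 100 mg twice daily | No antioxidant |
|---|---|---|---|
| Surgery | yes | yes | no arm |
| No surgery | yes | yes | no arm |

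Write each arm's expected change as T (time and regression to the mean) + S (surgery, where done) + A or E (ALA or vitamin E). This additive form is for illustration; allowing interaction does not help.

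- ALA minus vitamin E, within either row: A − E. Estimable.
- Surgery minus no surgery, within either column: S, always on top of an antioxidant. Estimable.
- A alone or E alone: in no randomised contrast.

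If A − E = 0, then A = E = 0 and A = E > 0 fit equally well. Vitamin E would resolve this only if its own effect were known, and the cited evidence on antioxidants is mixed. If A − E > 0, that is indirect evidence of an ALA effect, but still no comparison with taking nothing.

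**2. Potency.** Each agent has one regimen. The difference A − E belongs to agent and regimen together, so it can rank these two regimens but cannot say what strength is needed.

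**3. The plan's own sample size.** Sample size {14} gives mean changes in progressive motility (SD) of 12.05 (3.96), 6.56 (8.90), 4.15 (8.68) and 1.42 (7.60).

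- Grand mean = 24.18 / 4 = 6.045. Sum of squared deviations = 36.06 + 0.27 + 3.59 + 21.39 = 61.31.
- With the largest SD, 8.90, as common SD and n = 16, the noncentrality is 16 × 61.31 / 8.90² = 12.38. Power of the one-way F test (3 and 60 df, alpha 0.05) is 82.6%, and 16 is the smallest n above 80%.
- Dropout: 16 / (1 − 0.20) = 20 per arm, 80 in total.

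The stated 16 and 20 reproduce and are not in dispute. They size a comparison among four antioxidant-treated arms; no input describes an untreated change.

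**4. What the within-arm tests measure.** Each tests T + A or T + E without surgery, and T + S + A or T + S + E with it. Eligibility {10} requires abnormal semen quality, so T need not be zero.

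Illustration with A = E = 0. The non-drug mean change d is an assumption, 2 to 5 points; the SD range of 7.6 to 8.9 covers three of the four SDs in Sample size {14}. Two-sided paired t-test, alpha 0.05, n = 20, critical value 2.093 on 19 df, noncentrality d√n / SD:

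| d | SD | Noncentrality | Probability of significance |
|---|---|---|---|
| 2 | 8.9 | 2 × 4.472 / 8.9 = 1.00 | 16% |
| 2 | 7.6 | 2 × 4.472 / 7.6 = 1.18 | 20% |
| 5 | 8.9 | 5 × 4.472 / 8.9 = 2.51 | 66% |
| 5 | 7.6 | 5 × 4.472 / 7.6 = 2.94 | 80% |

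With 16 completers (critical value 2.131 on 15 df, √16 = 4), the same formula gives 13% to 69%. Either way, significance does not indicate an antioxidant effect at the nominal 5% error rate.

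**The case against.** The strongest reply is that the formal plan is sounder than its Discussion. Objectives {7} makes no necessity claim, Outcomes {12} defines the primary outcome as a change compared between groups, and Trial design {8} declares a superiority trial. Statistical methods {20a} puts between-group tests first and nowhere says that paired tests establish efficacy. The Abstract speaks only of an attempt. All of this stands, and it confines the correction to a few sentences. It does not rescue the Discussion's wording, which promises an answer that the design cannot give.

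Four stronger readings are tempting, and the documents do not support them.

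- *The potency question is a failed dose-finding aim.* Background and rationale {6a} asks whether ALA does better than traditional antioxidants, and Objectives {7} ties intensity to ALA or vitamin E. A stronger versus a traditional agent is the likely meaning, and the trial does randomise that comparison. What remains is that agent and regimen cannot be separated.
- *The planned surgical changes show how often surgery alone would give a significant result.* At n = 20 the planned changes give paired-test power of about 88% for surgical vitamin E and nearly 100% for surgical ALA. These figures cannot be read as rates under no antioxidant effect. Randomised arms with the same operation would then have equal expected changes, whereas the planned ones differ by 12.05 − 6.56 = 5.49 points. Nor is high power general: the non-surgical arms give 53% (ALA) and about 12% (vitamin E). Hence the illustration above uses an explicitly assumed change.
- *The cited literature shows that antioxidants do not help.* It is mixed, and the negative evidence is qualified by the absence of screening for oxidative stress.
- *The trial is uninformative.* Its randomised contrasts remain valid.

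That before-after results would be misread is a forecast, not something the plan states. It is a reason to fix their role in advance.

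**Conclusion.** The point holds for the conclusions that the trial announces, not for its randomised comparisons. Antioxidant versus none is not estimable with or without surgery. This follows from the arm definitions alone and needs no assumption. Potency can be answered only as a ranking of two fixed regimens.

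The within-arm tests cannot substitute. The 16% to 80% range shows how far they can mislead; it rests on the assumed non-drug improvement of 2 to 5 points, on normality and on 20 analysed men per arm, and it is not an estimate of what will happen here. The sample size and the objectives are not at fault on this point. Since the Discussion presents necessity as something that the trial will reveal, the correction should be made before results are reported.

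**What to change.** 1. In the Discussion paragraph of the Abstract and in the main Discussion, replace the necessity and potency claims with the two questions that the design can answer: (a) ALA versus vitamin E at the studied regimens, and (b) surgery versus no surgery when everyone takes an antioxidant. Necessity may stay as background motivation if the text says that this trial does not test it.
2. In Statistical methods {20a}, state that within-group changes are descriptive, reported as mean change with confidence interval, and support no claim of efficacy or necessity.
3. Objectives {7} needs no change on necessity. At most, clarify that different intensities means ALA versus vitamin E.

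Arms, regimens, sample size and randomised comparisons stay as they are. The cost is a few reworded sentences and a narrower claimed scope.

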## Trial status

The trial version is 1.0 and the protocol was approved on December 29, 2021. Recruitment will be started in June 2022 and the anticipated completion is December 2023.

## Data Availability

During the trial, all data will not be available to the public, but only to the research team.

## Abbreviations

ALA: Alpha-lipoic
ROS: Reactive oxygen species
OS: Oxidative stress
DR: Diameter at rest
TR: Time of reflux
PR: Progressive motility
NP: Non-progressive motility
FSH: Follicle-stimulating hormone
LH: Luteinizing hormone
E2: Estradiol
T: Testosterone
DFI: DNA fragmentation index
MDA: Malondialdehyde
TAC: Total antioxidant capacity
PUFAs: Polyunsaturated fatty acids
